## Abstract

**Background:**

Invasive mechanical ventilation contributes to bronchopulmonary dysplasia (BPD), the most common complication of prematurity and the leading respiratory cause of childhood morbidity. Non-invasive ventilation (NIV) may limit invasive ventilation exposure and can be either synchronized or non-synchronized (NS). Pooled data suggest synchronized forms may be superior. Non-invasive neurally adjusted ventilatory assist (NIV-NAVA) delivers NIV synchronized to the neural signal for breathing, which is detected with a specialized catheter. The DIVA (Diaphragmatic Initiated Ventilatory Assist) trial aims to determine in infants born 24^0/7^–27^6/7^ weeks’ gestation undergoing extubation whether NIV-NAVA compared to non-synchronized nasal intermittent positive pressure ventilation (NS-NIPPV) reduces the incidence of extubation failure within 5 days of extubation.

**Methods:**

This is a prospective, unblinded, pragmatic, multicenter phase III randomized clinical trial. Inclusion criteria are preterm infants 24–27^6/7^ weeks gestational age who were intubated within the first 7 days of life for at least 12 h and are undergoing extubation in the first 28 postnatal days. All sites will enter an initial run-in phase, where all infants are allocated to NIV-NAVA, and an independent technical committee assesses site performance. Subsequently, all enrolled infants are randomized to NIV-NAVA or NS-NIPPV at extubation. The primary outcome is extubation failure within 5 days of extubation, defined as any of the following: (1) rise in FiO_2_ at least 20% from pre-extubation for > 2 h, (2) pH ≤ 7.20 or pCO_2_ ≥ 70 mmHg; (3) > 1 apnea requiring positive pressure ventilation (PPV) or ≥ 6 apneas requiring stimulation within 6 h; (4) emergent intubation for cardiovascular instability or surgery. Our sample size of 478 provides 90% power to detect a 15% absolute reduction in the primary outcome. Enrolled infants will be followed for safety and secondary outcomes through 36 weeks’ postmenstrual age, discharge, death, or transfer.

**Discussion:**

The DIVA trial is the first large multicenter trial designed to assess the impact of NIV-NAVA on relevant clinical outcomes for preterm infants. The DIVA trial design incorporates input from clinical NAVA experts and includes innovative features, such as a run-in phase, to ensure consistent technical performance across sites.

**Trial registration:**

www.ClinicalTrials.gov, trial identifier NCT05446272, registered July 6, 2022.

## Administrative information

Note: the numbers in curly brackets as {} in this protocol refer to SPIRIT checklist item numbers. The order of the items has been modified to group similar items (see http://www.equator-network.org/reporting-guidelines/spirit-2013-statement-defining-standard-protocol-items-for-clinical-trials/)

## Introduction

### Background and rationale {6a}

Bronchopulmonary dysplasia (BPD) is the most common complication of prematurity and remains the leading respiratory cause of childhood morbidity [1–11]. BPD is an important determinant of the long-term neurodevelopmental outcome of infants and has societal impacts, including a cost of over $2.4 billion per annum in the United States [10–13]. Advances in neonatal care have led to increased survival among extremely premature infants (born less than 28 weeks’ gestation or 1000 g). Despite improved survival, BPD rates remain high [2].

Animal and clinical studies demonstrate that ventilator-induced lung injury (VILI) is a major factor in the development of BPD [14]. Both oxygen and positive pressure ventilation injure the immature preterm lung and cause VILI [15, 16]. Because even brief exposure to intubated positive pressure ventilation is injurious, avoiding invasive mechanical ventilation is the most widely acknowledged strategy to prevent VILI and BPD. Therefore, time on ventilators and rates of successful extubation are important endpoints of therapy.

Currently, no consensus evidence-based approaches exist to identify infants who can be successfully extubated. Therefore, extubation failure occurs in as many as 50% of infants [17, 18]. Exposure to multiple courses of mechanical ventilation is common and associated with increased risk for BPD [19, 20]. Intubation is a high-risk procedure, with adverse events occurring in 19% and severe events in 4% [21]. Recurrent extubation/reintubation risks airway damage and is associated with subglottic stenosis [22]. Therefore, preventing extubation failure requiring reintubation is a clinically relevant target to prevent acute and chronic airway and lung injury in extremely preterm infants [23–25].

The Diaphragmatic Initiated Ventilatory Assist (DIVA) trial is an unblinded, pragmatic, multicenter phase III randomized clinical trial in extremely preterm infants 24^0/7^–27^6/7^ weeks gestational age to determine if non-invasive neurally adjusted ventilatory assist (NIV-NAVA), compared with non-synchronized nasal intermittent positive pressure ventilation (NS-NIPPV), prevents extubation failure within 5 days (120 h) of extubation from mechanical ventilation.

### Objectives {7}

The primary objective is to compare rates of extubation failure within 5 days of extubation between extremely preterm infants treated with NIV-NAVA to those treated with NS-NIPPV.

The secondary objective is to compare respiratory and safety outcomes through 36 weeks postmenstrual age (PMA) among infants treated with NIV-NAVA vs. NS-NIPPV.

### Trial design {8}

The DIVA trial is a prospective, pragmatic, multi-site, phase III randomized trial to investigate the effectiveness of NIV-NAVA vs. NS-NIPPV in preventing extubation failure within 5 days of extubation. After sites demonstrate proficiency managing NIV-NAVA during a run-in phase of 3–10 infants per site, infants will be randomized to receive either NIV-NAVA or NS-NIPPV following extubation, with a primary outcome of extubation failure within 5 days of extubation. The randomization phase uses a two-arm group sequential design (GSD) with two interim looks. Treatment allocation is blinded, though implementation of intervention is not blinded. Infants enrolled during the run-in phase will not be included in the primary or secondary outcomes analysis.

## Methods: participants, interventions, and outcomes

### Study setting {9}

The study will occur in neonatal intensive care units in the United States and Canada. A list of participating sites is available at https://clinicaltrials.gov/.

### Eligibility criteria {10}

Inclusion criteria:Gestational age of 24–27^6/7^ weeks at birthIntubated in the first 7 days of lifeUndergoing extubation following at least 12 h of invasive mechanical ventilationPostnatal age < 28 days at the time of extubation

Exclusion criteria:Major congenital anomalies, including pulmonary hypoplasiaNeurologic disorders affecting respiratory drive (other than apnea of prematurity)Esophageal bleeding or other contraindications to naso/orogastric catheter placementCurrent weight < 500 g (based on Edi catheter approval)Study ventilator not available at time eligibility criteria are metPlanned surgery or invasive procedure within 5 days of extubationInformed consent not provided

### Who will take informed consent? {26a}

A member of the study team will approach parents to offer study participation and obtain informed consent. A DIVA trial educational video was developed to augment this discussion and allow families to review key information about the trial. https://youtu.be/zqzZYImXaHU

### Additional consent provisions for collection and use of participant data and biological specimens {26b}

The informed consent form states that participant data may be used to support secondary research analyses. A separate informed consent will be obtained for any ancillary studies that require additional research procedures. No biological specimens are collected in the trial.

## Interventions

### The explanation for the choice of comparators {6b}

Meta-analysis favors NIPPV over continuous positive airway pressure (CPAP) to prevent extubation failure in preterm infants. Data from clinical trials suggest that synchronized support is beneficial, but effective methods of achieving this synchrony have been limited until recently. Preliminary data of extubation practice at the original DIVA trial study sites showed an equal use of NIV-NAVA (35%) and NS-NIPPV (38%) for preterm infants (remainder CPAP or high-flow nasal cannula) (Table 1). These data confirm clinical and ethical equipoise for the control intervention at participating sites.

**Table 1 Tab1:** Extubation failure rates within 5 days for infants 24–27^6/7^ weeks gestational age at DIVA trial sites

Mode	Extubation failure		
	Yes	No	Total
NIV-NAVA	7 (18.9%)	30 (81.1%)	37
NIPPV	17 (40.5%)	25 (59.5%)	42

### Intervention description {11a}

There are 2 phases in the trial. First is an initial run-in phase, in which all enrolled (consented) and eligible infants at each site are allocated to NIV-NAVA to ensure site-level baseline NIV-NAVA technical proficiency and protocol adherence. Following this phase, sites progress to the randomization phase, where all enrolled infants are randomly allocated in a 1:1 fashion to either NIV-NAVA or NS-NIPPV (Fig. 1).

**Fig. 1 Fig1:**
[figure not shown]
Flow diagram for screening, consent, and treatment allocation for DIVA trial. NICU, neonatal intensive care unit; GA, gestational age; NIV-NAVA, non-invasive neurally adjusted ventilatory assist; ASAP, as soon as possible; NIPPV, nasal intermittent positive pressure ventilation

### Respiratory management

Protocol-mandated aspects of respiratory management during the intervention period include the following:Infants will be managed according to their allocated support mode for 5 days (120 h) after extubation, with no cross-over between groupsNIV-NAVA will be delivered using the Servo-I, Servo-N, or Servo-U with the associated Edi catheter. All of these have FDA clearance for neonates weighing > 500 gInfants in the control arm will be managed using an FDA-approved respiratory device, per the study unit’s standard of careFor both treatment groups, respiratory support will be provided using an interface with FDA approval or clearance to provide continuous positive pressure for preterm infants. RAM cannula and other non-approved interfaces, therefore, will not be usedAll infants must be treated with systemic (enteral or parenteral) caffeine throughout the study intervention periodVentilator settings will be titrated according to local unit norms within the allowable DIVA protocol settings (Table 2). These reflect variations in site practice across all DIVA trial sites. Sites do not need to escalate parameters to the maximal values provided. Guidelines for escalating and weaning ventilator support in both arms are provided in the manual of operations

**Table 2 Tab2:** Range of allowable NIV-NAVA and NS-NIPPV settings

	**Intervention arm: NIV-NAVA**	**Control arm: NS-NIPPV**
PEEP	5–10 cm H_2_O	5–10 cm H_2_O
PIP	N/A, backup PIP 15–30 cm H_2_O	15–30 cm H_2_O
Rate	N/A, backup rate 10–60	10–60

### Criteria for discontinuing or modifying allocated interventions {11b}

Study infants should remain on the allocated mode of support throughout the entire 5-day intervention period. However, if an infant has been weaned to minimal settings for the allocated mode of support with FiO_2_ 21% for at least 12 h, they may be weaned to CPAP per clinical judgement. Weaning an infant to CPAP before meeting these criteria for at least 12 h is a protocol violation.

### Strategies to improve adherence to interventions {11c}

Every effort will be made to allocate and initiate study treatment for enrolled (consented) and eligible infants as close to the time of extubation as possible, with no more than 2 h between extubation and initiation of allocated respiratory therapy. In the case of an unplanned extubation for an infant with informed consent, if the clinical team determines to provide a trial of non-invasive support, the infant will be allocated to study treatment as soon as possible, no later than 2 h after extubation.

### Internal monitoring

The site principal investigator (PI) will be responsible for internally monitoring each infant meeting the extubation failure criteria. The site PI will review the ventilator management for that infant and confirm whether ventilator settings were adjusted appropriately per unit norms and within the allowable DIVA trial parameters.

### External monitoring

The DIVA technical committee will assess all sites’ technical performance during the trial for infants on both NIV-NAVA and NS-NIPPV. During the run-in phase, each site’s performance with NAVA will be assessed using ventilator screenshots respiratory settings data (Table 3). Sites will not be able to randomize infants until NAVA proficiency is demonstrated. In the randomization phase, sites will continue to monitor and evaluate their performance in both arms of the study. The technical committee will monitor the first six randomized infants, and a random 10% will be monitored thereafter. The technical committee will use the run-in phase approach to monitor infants treated with NIV-NAVA in the randomization phase (Table 3). In addition, NIPPV settings and clinical data will also be evaluated systematically for infants randomized to NS-NIPPV.

**Table 3 Tab3:** NIV-NAVA ventilator screen shots assessed by technical committee

Parameter assessed	Interval
Edi catheter screen	Once
Alarm limit screen	Once
Time in back up and FiO_2_	3-h trend
Time in back up and FiO_2_	24-h trend
Edi peak, PIP, respiratory rate	3-h trend
Edi peak, PIP, respiratory rate	24-h trend
Ventilator setting/parameter screen	Once

### Relevant concomitant care permitted or prohibited during the trial {11d}

Beyond specified protocol-mandated aspects of care, infants will be managed according to local clinical protocols for respiratory medications and titrating supplemental FiO_2_ to maintain local SpO_2_ targets. The executive committee will determine whether concurrent enrollment in other site studies is acceptable.

### Provisions for post-trial care {30}

Enrolled infants will be managed as directed by the local clinicians following the 5-day intervention period. Secondary and safety outcomes will be ascertained until 36 weeks’ PMA, death, or discharge (whichever comes first).

## Outcomes {12}

### Primary study endpoint

The primary study endpoint is extubation failure. Extubation failure is defined when an infant is on the allocated mode of respiratory support and meets any of the following four criteria: (1) rise in FiO_2_ at least 20% from pre-extubation value for > 2 h to maintain local SpO_2_ targets, (2) pH ≤ 7.20 or pCO_2_ ≥ 70 mmHg; (3) > 1 apneic event requiring positive pressure ventilation (PPV) within 6 h or ≥ 6 apneic events requiring stimulation within 6 h; (4) emergent intubation by the clinical team for cardiovascular instability or surgery; (5) any other intubation.

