### Methods in analysis to handle protocol non-adherence and any statistical methods to handle missing data {20c}

A modified “as-randomized” analysis (or “intention-to-treat” analysis) will be used. One pre-specified modification to the analytic set is the exclusion of randomized infants who are not subsequently extubated for new/emergent conditions not known at time of randomization. This number is expected to be minimal and will be closely monitored. All other infants will be included in the analysis under standard ITT assumptions.

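### The primary endpoint counts extubation failure only while the infant is on the allocated mode; this conflicts with the 5-day objective and can dilute or bias the result in either direction

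*Protocol article*

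**What the plan says.** The Primary study endpoint section of the protocol article opens its definition with "Extubation failure is defined when an infant is on the allocated mode of respiratory support". The word 'and' then joins this to the criteria. These are a sustained rise in FiO2, blood gas limits, apnoea counts, emergent intubation for cardiovascular instability or surgery, and "any other intubation".

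Other sections state the outcome without the condition. Background and rationale {6a} asks whether NIV-NAVA "prevents extubation failure within 5 days (120 h) of extubation from mechanical ventilation". Objectives {7} and the Methods part of the abstract also set failure within 5 days of extubation and do not mention current support.

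The protocol itself foresees time off the allocated mode inside that window:

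- Section {11b}: infants who meet the weaning criteria are not held on the mode; "they may be weaned to CPAP per clinical judgement".
- Section {11b} also foresees early departures: "Weaning an infant to CPAP before meeting these criteria for at least 12 h is a protocol violation".
- Section {11c}: there may be a gap, with "no more than 2 h between extubation and initiation of allocated respiratory therapy".
- Respiratory management: cross-over is prohibited, but no outcome rule is given if it happens.

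On the analysis set, section {20c} excludes only randomised infants not extubated because of new or emergent conditions. For the rest: "All other infants will be included in the analysis under standard ITT assumptions".

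**The concern.** An infant who has left the allocated mode stays in the denominator. Under the literal endpoint wording, what happens to that infant while off the mode does not enter the numerator. This includes reintubation, the event that the trial exists to prevent. Two analysts, one working from the abstract and one from the endpoint section, could code the same infant differently.

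The condition also works against the reason given for the endpoint. The rationale and the Discussion prefer physiological criteria to reintubation because clinicians are unblinded and their decisions could differ by arm. Leaving the mode is also a decision of unblinded clinicians, and under this wording it determines when events stop counting. The two arms use different equipment (a specific ventilator family and catheter against any approved device under unit practice), so departures need not be equal. If they are equal, the effect is diluted. If they are not, the estimate can move either way.

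**Working it through.** **1. What follows from the text.** Take an infant weaned to CPAP at hour 60 under {11b} and reintubated at hour 80.

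- Abstract, Background, Objectives: a failure, because the event falls within 120 h of extubation.
- Primary study endpoint: not a failure, because the infant is not on the allocated mode. The clause on any other intubation sits under the same condition and does not rescue the case.
- Section {20c}: the infant is in the analysis set.

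No section of the article settles this conflict.

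**2. The plan's own sample size.** For 35% vs 20%, two-sided 0.05 and 90% power, the continuity-corrected fixed sample is 396. O'Brien-Fleming-type spending at 50%, 75% and 100% inflates it by 1.018: 396 × 1.018 ≈ 403, against the stated 406. Then 406 × 1.15 = 466.9, rounded up to 467; 467 / 0.98 = 476.5, and the next equal split is 478. The plan's figures reproduce, and they do not change under the fix.

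**3. Equal loss in both arms.** The share of failures that occur off the mode is not in the documents, so it is assumed. Effective n per arm = 478 × 0.98 / 1.15 / 2 ≈ 204. Fixed-sample pooled z-test: power = Φ((d − 1.96·SE0) / SE1), with SE0 the pooled and SE1 the unpooled standard error.

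| Failures not counted | Observed rates | d (points) | Power |
|---|---|---|---|
| 0% | 35.0% vs 20.0% | 15.0 | 92.7% |
| 10% | 31.5% vs 18.0% | 13.5 | 88.7% |
| 20% | 28.0% vs 16.0% | 12.0 | 83.5% |

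Check of the last row: SE0 = 0.0410, SE1 = 0.0406, (0.120 − 0.0805) / 0.0406 = 0.97, Φ = 0.835.

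**4. Loss in one arm only, same method.** A 20% loss in control alone gives 28% − 20% = 8.0 points and 47.2% power. A 20% loss in NIV-NAVA alone gives 35% − 16% = 19.0 points, an overstatement.

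**5. No true difference.** Let f be the share leaving the mode and h the risk of a first failure after leaving. The spurious benefit is h × (f in NIV-NAVA − f in control). The true rate is taken as 30% in both arms, with 234 per arm (478 × 0.98 / 2), and the upper-side rejection probability is nominally 2.5%.

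| f, NIV-NAVA vs control | h | Spurious benefit (points) | False superiority |
|---|---|---|---|
| 10% vs 3% | 10% | 0.7 | about 3.6% |
| 10% vs 3% | 50% | 3.5 | about 13% |
| 5% vs 5% | 50% | 0 | 2.5% |
| 3% vs 10% | 50% | −3.5 | about 0.2% |

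Check of the first row: SE ≈ 0.0421, (0.007 − 0.0825) / 0.0421 = −1.79, Φ = 0.036. The second row is 13.2% with the planned group sequential boundaries. With about 204 effective infants per arm it is about 12%, and with a 35% rate as well it is 11.3%.

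**The case against.** The strongest reply is that the on-mode clause may only describe the expected state, since the protocol requires the allocated mode for the full 120 h. The inclusion of any other intubation suggests that the authors meant to capture all reintubations. That may be the intent, but the text does not say so, and {11b} expressly lets infants leave the mode.

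Second, {20c} concerns who is analysed and the endpoint section concerns what counts as an event, so strictly the analysis set is not contradicted. This is correct. The conflict lies in the event definition, which brings an on-treatment element into an as-randomised comparison.

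Third, the protocol limits the problem. Ventilator availability is confirmed before randomisation, the catheter is designed for 5 days of use, and there are a run-in phase and audits. Permitted weaning needs minimal settings and FiO2 21% for at least 12 h, so later failures in those infants may be few. The gap of up to 2 h is an upper limit and adds little. All of this stands, and it makes the scenarios with 50% later failure a high end that would need violations, device loss or cross-over.

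A reader might infer more than the documents support:

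- That off-mode infants cannot fail at all. They can fail while on the mode, and a violation matters only if it takes them off it.
- That the result is biased towards NIV-NAVA. The documents give no departure rates by arm, so the direction is unknown.
- That never-extubated infants score as successes in the conventional intention-to-treat sensitivity analysis. Section {20a} does not state their coding, which an analysis plan would normally set.

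**Conclusion.** The point holds in a limited form. The endpoint section states a rule that conflicts with the abstract, the Background and the Objectives. Followed literally, it leaves out failures, including reintubations, that occur off the allocated mode within 120 h. This is more than missing detail, because the stated rule gives the wrong classification for the trial's own objective.

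The consequence is that the result can be diluted or biased, not that it will be. The effect on the estimate ranges from negligible, if few infants fail after leaving the mode, to several points of the 15-point target if losses are large or unequal. All of these sizes rest on assumed departure rates and later-failure risks. Confidence is high in the textual conflict and low in any particular size or direction of bias.

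**What to change.** Reconcile the abstract, the Objectives and the Primary study endpoint section. Remove the on-mode condition and define failure as any listed criterion met from extubation to 120 h, regardless of current support. The same edit should align the list of criteria: the endpoint section announces four and lists five, and the abstract lacks the fifth. Keep the on-mode version as a supplementary analysis only. Optionally, state whether death by 120 h without another criterion counts as failure; this is a minor gap.

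The cost is small. The sample size stays at 478. Table 5 already collects the failure criteria and intubations daily for the first 5 days after allocation. Sites must keep recording the criteria after an infant leaves the mode. The change should be settled before outcomes are coded by arm, and before an interim look if one is still ahead, because both interim analyses use this endpoint.
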